### 2.4. Recruitment

A single midwife will take charge of maternal education in the CMU Puerto Real, which includes the Ribera del Muelle Health Centre where there are three paediatricians, and the Rio San Pedro Health Centre where there is one. Therefore, all pregnant women will receive exactly the same information about the intervention. After birth, the parents will decide in which of the six paediatricians of the BHZ of Puerto Real they will register their children, and we cannot interfere in that decision.

The study population of the control group will be constituted by two-year-old children of two quotas of the Basic Health Zone of Puerto Real. The paediatricians have employment stability for at least the expected duration of the study and have agreed to participate. The inclusion in the study and the data collection will be carried out in the health controls at 2 years of age at the same time as the intervention in pregnant women begins, so that neither mothers during pregnancy nor infants after delivery will have been influenced by the intervention. Once the intervention ends, their results will be analyzed from the data obtained from the mother–child pairs.

Following the above criteria, all newborns assigned to the four pediatricians of the unit that meet the inclusion criteria will be included in the intervention group. Two paediatricians from the same unit will also participate in the data collection for the control group. Including a greater number of pediatricians is necessary to obtain the calculated sample of the intervention group, due to the decrease in the birth rate observed in recent years. Inclusion in the study will be done at the first pediatric visit of the newborn.

The inclusion criteria are: two-year-old infants whose pregnancy begins in the 14 months following the start of the intervention, and whose mothers have made the complete follow-up of their pregnancy in the Care Process of Pregnancy Childbirth and Puerperium and begun the monitoring of child health controls of the Andalusian Children and Adolescents Health Program in our unit. The exclusion criteria are: infants whose parents do not authorize their participation in the study in writing.

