## Abstract

(1) *Background*: Obesity is a global health problem, and its prevention must be a priority goal of public health, especially considering the seriousness of the problem among children. It is known that fetal and early postnatal environments may favor the appearance of obesity in later life. In recent years, the impact of the programs to prevent obesity in childhood has been scarce. The aim of this research is to evaluate the effectiveness of an intervention based on the concept of early programming. (2) *Methods*: Non-randomized controlled trial design. Inclusion criteria are: two-year-old infants whose gestational period begins in the 14 months following the start of the intervention, and whose mothers have made the complete follow-up of their pregnancy in the same clinical unit of the study. The intervention will be developed over all the known factors that affect early programming, during pregnancy up to 2 years of life. Data will be collected through a data collection sheet by the paediatricians. A unibivariate and multivariate analysis of the data will be carried out. (3) *Ethics and dissemination*: The trial does not involve any risk to participants and their offspring. Signed informed consent is obtained from all participants. Ethical approval has been obtained. (4) *Results*: It is expected that this study will provide evidence on the importance of the prevention of obesity from the critical period of the first 1000 days of life, being able to establish this as a standard intervention in primary care.

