The project’s global hypothesis is that an intervention in the first 1000 days of life on the early programming factors related to childhood obesity will achieve more adequate early programming and will decrease the prevalence of childhood obesity. The risk of developing obesity in childhood will be lower when the number of factors accumulated in the individual in this critical first phase is decreased. This improvement in early metabolic programming will be reflected in a lower percent of body fat mass at 2 years of age, compared to the control group.

The aim of the project is to evaluate the effectiveness of a combined multifactorial educational and care intervention for preventing obesity and overweight in childhood, based on the concept of early programming, and developed during pregnancy and the first 2 years of life (the first 1000 days) by a multidisciplinary group in primary care. The specific objectives are:

To analyse the body fat mass at 2 years of age in a control group of children who reach this age between November 2017 and June 2019, belonging to two pediatric quotas of the Basic Health Zone (BHZ) of Puerto Real.

To analyse the body fat mass at 2 years of age in the intervention group of children, whose pregnancies begin between January and December 2018, belonging to four pediatric quotas of the BHZ of Puerto Real. 

To compare the body fat mass at 2 years of age between the control and intervention groups.

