### 2.7. Intervention 

The intervention is being carried out during pregnancy and the following 2 years after birth. The intervention period during pregnancy began, for each individual patient, when they went to their first visit related to the Care Process of Pregnancy, Childbirth and Puerperium Program during the period of time between January 2018 and February 2019. This first visit is carried out by the midwife in charge (Clinical Managing Unit) and is integrated within the standard medical visits and workshops, although reinforced by a specific workshop, purely based on the intervention scheme, at the beginning of the patient’s pregnancy. 

Three workshops take place during this period. They happen once a month for a total of two hours at a time. In each workshop, the patients are handed a fully informed leaflet in which they can learn about the information given and write personal notes at their discretion. 

Workshop number one, specifically created for the intervention period, takes place before the 12th week of pregnancy is reached. To begin the workshop, a 15- to 20-min slideshow is shown to explain the “early programming” concept and its close relation to childhood obesity. Immediately after this, the attendees will be fully informed about the importance of physical exercise, quitting toxic habits and creating a healthy eating plan for the entire family. 

At the second workshop, which has to be completed between the 16th and 18th weeks of pregnancy, the information provided is related to the specific healthcare and healthy habits that a pregnant woman should embrace, considering the changes she will experience.

Finally, on the third workshop, carried out between the 30th and 32nd weeks of pregnancy, the attendees will learn about the special characteristics of care related to newborns. To begin, a 20-min slideshow, in which the postnatal programming and its different factors are explained in detail, will be shown. After that, exclusive breast feeding will be explained and promoted as the preferable option. The child and adolescent health scheme planed by the Andalusian health authorities will also be introduced during this session. 

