The first visit within the pregnancy, birth and puerperium scheme is carried out between the 4th and 7th week of pregnancy. It is a 30-min visit in which the pregnant woman will receive an informative leaflet with general recommendations about a healthy pregnancy, where she will be introduced to the concept of early programming and its close relation to childhood obesity. Those pregnant women considered obese, who admit smoking, or who are believed to be unhealthy dieters, will be encouraged to take on the first workshop. 

Subsequent visits will monitor the risk factors, including whether new factors arise or persist, in which case workshop number one will be offered again or as a first time informative session. Early programming and childhood obesity will be the main and consistent ideas to be reinforced on each visit. The basic recommendations and lifestyle habits proposed to each pregnant woman will be related to these core concepts. 

Both workshops two and three will be offered to all pregnant women in the program. Those in the 14th–16th week of pregnancy will be encouraged to attend workshop number two, and those in the 30th-32nd week will be offered workshop number three.

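### No historical control can meet the inclusion criteria as written, so the pregnancy follow-up condition in effect applies to one group only, and both cohort windows are stated inconsistently

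*Protocol article*

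**What the plan says.** Section 2.4 (Recruitment) states the inclusion criteria once: "two-year-old infants whose pregnancy begins in the 14 months following the start of the intervention, and whose mothers have made the complete follow-up". The follow-up meant is that of pregnancy care, and the criteria add that child health monitoring has begun in the unit. The Abstract repeats the onset clause without limiting it to a group, "two-year-old infants whose gestational period begins in the 14 months following the start of the intervention", and joins it to complete pregnancy follow-up in the study's clinical unit. Where section 2.4 applies these criteria, it does so for newborns entering the intervention group.

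Controls are described differently: "The study population of the control group will be constituted by two-year-old children of two quotas of the Basic Health Zone of Puerto Real". The same section requires that neither their gestation nor their infancy was influenced by the intervention.

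The dates are given in several places:

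- **Intervention group, specific objectives (section 1):** children "whose pregnancies begin between January and December 2018, belonging to four pediatric quotas of the BHZ of Puerto Real".
- **Intervention group, Abstract and section 2.4:** pregnancies beginning in the 14 months after the start.
- **Intervention group, section 2.7:** the intervention began for each woman "when they went to their first visit related to the Care Process of Pregnancy, Childbirth and Puerperium Program". The dates set for these first visits are "during the period of time between January 2018 and February 2019". As to gestational age, the visit "is carried out between the 4th and 7th week of pregnancy".
- **Control group, specific objectives:** children reaching age 2 from November 2017 to June 2019.
- **Control group, section 2.1:** children reaching age 2 during 2018.

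**The concern.** In a non-randomized comparison with historical controls, the eligibility rules are the main protection against comparing different kinds of family. If one group must have complete pregnancy follow-up in the unit and the other need not, the groups can differ for reasons unrelated to the intervention. In the intervention group, moreover, completion is known only after the intervention has started, because the intervention is delivered through the pregnancy visits and workshops (section 2.7). Selecting on something that happens after exposure begins is a recognised source of bias. Section 2.11 relies on the two groups coming from a homogeneous population, and unequal entry rules weaken that argument.

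The conflicting windows are a second problem. They leave open which children at the edges belong to each group, and that should be settled before outcomes are known.

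**Working it through.** **1. Can a control child meet the onset clause?**

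Inputs: the two control windows (objectives and section 2.1). The start of the intervention is taken as 1 January 2018, the opening of the first-visit window in section 2.7. Gestation length is assumed: 280 days from last menstrual period at term.

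Latest onset = latest birth date − gestation.

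- Objectives: age 2 by 30 June 2019 means birth by 30 June 2017. Less 280 days, the latest onset is 23 September 2016, which is 465 days (about 15 months) before 1 January 2018.
- Section 2.1: age 2 by 31 December 2018 means birth by 31 December 2016. The latest onset is 26 March 2016, 646 days before.
- Sensitivity, using the later (objectives) window: counting 266 days from conception, the gap is 451 days. With birth at 24 weeks (168 days) it is still 353 days.

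No assumption tried brings a control pregnancy into the 14-month window. Since the clauses are joined, the criteria as written can be met only by intervention children.

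**2. Do the intervention windows agree?**

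- Onsets January to December 2018: 365 days.
- Onsets in 14 months from 1 January 2018: to 28 February 2019, 424 days.
- Difference: 424 − 365 = 59 days.

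The section 2.7 window counts first visits, not onsets. With a first visit at 4 weeks 0 days to 7 weeks 6 days (28 to 55 days):

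- Onsets from 1 January to 31 December 2018 give first visits from 29 January 2018 (1 January + 28 days) to 24 February 2019 (31 December + 55 days). This broadly fits January 2018 to February 2019.
- In reverse, first visits from 1 January 2018 to 28 February 2019 allow onsets from 7 November 2017 (− 55 days) to 31 January 2019 (− 28 days), so there is some spill at both ends.
- An onset on 1 February 2019 meets the 14-month clause, but its first visit is on 1 March 2019 at the earliest, outside the section 2.7 window.

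The objectives and section 2.7 are therefore broadly compatible. The clear contradiction is between the objectives (12 months of onsets) and the Abstract and section 2.4 (14 months of onsets). The 14 months may have been carried over from visits to onsets.

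**3. How many children are affected?**

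Section 2.2 expects about 50 newborns per quota per year. This is consistent with its 320 births over six quotas: 320/6 = 53.3.

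Expected births = quotas × 50 × months/12.

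| Group | Window | Expected | After 15% loss (section 2.5) | Planned |
|---|---|---|---|---|
| Intervention, 4 quotas | 12 months | 200 | 170 | 150 |
| Intervention, 4 quotas | 14 months | 233 | 198 | 150 |
| Control, 2 quotas | 12 months (2018) | 100 | 85 | 100 |
| Control, 2 quotas | 20 months (Nov 2017 to Jun 2019) | 167 | 142 | 100 |

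The windows differ by about 33 expected births for the intervention group and about 67 for controls, before loss.

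**The case against.** The strongest reply is that the onset clause was plainly meant for the intervention cohort and that the follow-up clause was meant for everyone. The article never says that controls are exempt. Controls are treated as mother–child pairs, and their data come partly from the mothers' records (section 2.9). An unwritten parallel rule cannot be excluded. This stands as a limit on the point: the defect is in what is written, not proof of what was done. It does not remove the defect, because the criteria as printed exclude the entire comparator and no pregnancy-care condition for controls is stated.

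A reader might go further and infer that the filter keeps only adherent mothers in the intervention group and so favours the intervention. The documents do not support that:

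- Complete follow-up may describe where care took place rather than attendance at every visit. The protocol provides for a missing last pregnancy weight (section 2.8.1) and a missed puerperal visit (section 2.9), and workshops are offered, not required (section 2.7).
- Controls are also selected on attendance, since they enter at the 2-year health check, whereas intervention children enter at the first paediatric visit.
- Any size is guesswork. The shift would be the share excluded times the difference in body fat. Assuming 10–30% excluded and 0.3–0.5 SD gives 0.10 × 0.3 = 0.03 to 0.30 × 0.5 = 0.15 SD, but neither input is in the documents. The filter produces no such one-sided shift if the clause concerns only place of care and this does not differ between groups, or if controls follow the same rule.

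A reader might also count three conflicting intervention windows. There are two for onset; the section 2.7 window broadly fits the objectives. Nor is the planned intervention sample threatened, since both windows yield more than 150 after loss.

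**Conclusion.** The point holds as a defect in the eligibility text. No control can meet the stated inclusion criteria: the latest control pregnancy precedes January 2018 by about 15 months at term, and by almost a year even with birth at 24 weeks. The complete-follow-up condition is therefore stated in effect for the intervention group alone. Taken literally, the groups are selected by different rules, one of them resolved only after the intervention has begun. This may bias the comparison; its direction and size are not established.

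The intervention onset window is contradictory (12 against 14 months, about 200 against 233 births), and so is the control window (20 against 12 months, about 167 against 100 children). These counts rest on 50 births per quota per year spread evenly over the year. The date conclusions rest on a January 2018 start and the gestation lengths shown.

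**What to change.** - Write eligibility separately for each group.
- State one intervention window, defined either by first pregnancy visit or by pregnancy onset, identically in the Abstract, the specific objectives, section 2.4 and section 2.7.
- State one control window, identically in the specific objectives and section 2.1.
- Apply the same pregnancy-care and unit-registration rule to both groups, checked in the Diraya records that section 2.9 already uses for controls. A first pregnancy visit in the unit is preferable, because it is fixed at the start of pregnancy care and does not depend on later attendance.
- Define complete follow-up and keep that subset, in both groups, as a sensitivity analysis.
- Report how many mother–child pairs each rule removes, by group.

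The cost is rewording and a record check for controls. Some controls may be lost. That matters most with the 12-month control window, which yields only about 100 children before any loss.

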### 2.5. Sample Size Estimation

An intentional sampling has been performed on a population of 320 births over a period of time of 1 year (2017) in the geographical situation of Puerto Real. The source of information was historical data collected from primary care management of the Bahía de Cádiz-La Janda District. It is estimated that the control group will be formed of 100 sample units and the experimental group of 150 sample units. For this configuration, assuming the randomness of the sample collected, the precision errors will be approximately 9% and 7% respectively (from the experimental group and the control group). These error levels were calculated by establishing a significance level of 95% (α = 0.05) and assuming a loss rate of 15%.

We estimate that this number of cases will guarantee the level of confidence and power necessary for statistical analysis.

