#### 2.8.2. Dependent Variables

BMI at 2 years of life.Percentage of fat mass at 2 years of life.

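### The precision errors in Section 2.5 are attached to the wrong groups, and a one-group margin does not support the claim that power is guaranteed

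*Protocol article*

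**What the plan says.** Section 2.5 of the protocol article fixes the group sizes: "It is estimated that the control group will be formed of 100 sample units and the experimental group of 150 sample units". The next sentence gives the precision: "the precision errors will be approximately 9% and 7% respectively (from the experimental group and the control group". It is said to come from "establishing a significance level of 95% (α = 0.05) and assuming a loss rate of 15" percent. The population named is a single year of births: "An intentional sampling has been performed on a population of 320 births over a period of time of 1 year (2017"). The section closes with a statement about power: "We estimate that this number of cases will guarantee the level of confidence and power necessary for statistical analysis".

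The objectives at the end of Section 1 include comparing body fat mass at 2 years between control and intervention groups. Section 2.8.2 lists two dependent variables, BMI and "Percentage of fat mass at 2 years of life". Both are continuous.

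**The concern.** Three things look wrong.

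- The larger group (150) is given the larger error and the smaller group (100) the smaller one.
- The printed magnitudes appear to rely on a finite population of 320. Those are the 2017 births of the whole Basic Health Zone, with six quotas (Sections 2.2 and 2.5). The children studied come from other periods and, for controls, from only two quotas.
- The text moves from a percentage margin within one group to a claim of adequate power for a difference between two groups in a continuous outcome. The first does not imply the second.

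At stake is the article's only justification of sample size. As written, one pair of figures is wrong, the precision may be flattered, and a reader is told that power is assured without any figure bearing on the planned comparison.

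**Working it through.** **Inputs.** From Section 2.5: control 100, experimental 150, N = 320, α = 0.05, loss 15%. Loss leaves 100 × 0.85 = 85 and 150 × 0.85 = 127.5 (written as 127 below). Assumed, because the article does not give them: two-sided z = 1.96, p = 0.5, and the formula itself.

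**Step 1. Reproduce the printed figures.** Margin = 1.96 × √(p(1−p)/n), multiplied by √((N−n)/(N−1)) if a finite population correction is used.

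- Control, n = 85: 1.96 × √(0.25/85) = 10.63%. The correction is √(235/319) = 0.858, giving **9.12%**.
- Experimental, n = 127.5: 1.96 × √(0.25/127.5) = 8.68%. The correction is √(192.5/319) = 0.777, giving **6.74%**.

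The magnitudes 9 and 7 appear, but with control at 9 and experimental at 7.

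**Step 2. Can the labels be right as printed?** Without a correction, the ratio of experimental to control margin is √(100/150) = 0.82 for every p and z. The correction lowers it further. The printed ratio is 9/7 = 1.29. A search over p from 0.05 to 0.50, with and without loss and correction, found no case that rounds to 9% experimental and 7% control. Loss in the experimental group alone does not reverse the order either, since 127.5 still exceeds 100.

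**Step 3. Is the correction certain?** No. Uncorrected margins can also round to 9% and 7%, again with control the larger:

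| Setting | Control | Experimental |
|---|---|---|
| p = 0.5, 15% loss, corrected for N = 320 | 9.12% | 6.74% |
| p = 0.23, 15% loss, no correction | 8.95% | 7.30% |
| p = 0.30, no loss, no correction | 8.98% | 7.33% |
| p = 0.5, 15% loss, no correction | 10.63% | 8.68% |

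The first row uses every input that Section 2.5 states plus the conventional p, so it is the natural reading.

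**Step 4. Would the correction be valid?** Intervention children come from pregnancies beginning in 2018 (Section 1), so none is among the 2017 births. Controls reach age 2 between November 2017 and June 2019 (Section 1), so they were born about November 2015 to June 2017. Under Section 2.1 they turn 2 during 2018, so they were born in 2016. At most the controls born January to June 2017 are among the 320.

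**Step 5. What the numbers give for the planned comparison.** With outcomes in SD units and independent children, the standard error is √(1/85 + 1/127.5) = 0.140.

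- Detectable difference, 80% power: (1.96 + 0.84) × 0.140 = **0.39 SD**; 90% power: (1.96 + 1.28) × 0.140 = 0.45 SD.
- 95% confidence interval half-width: 1.96 × 0.140 = **0.27 SD**.
- With no loss, √(1/100 + 1/150) = 0.129, giving 0.36 SD at 80% power and a half-width of 0.25 SD.
- Power at assumed differences of 0.2, 0.3, 0.4 and 0.5 SD (85 against 127.5): about 30%, 57%, 82% and 95%.

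**The case against.** The strongest reply is that much of this is minor or inferred. The swap is visible from the preceding sentence and alters no group size or analysis. The article names no formula, so the finite population correction is a reconstruction, and 320 may be only a planning count of annual births. The power sentence is worded as an estimate. An effect size, SD and power value may stand in a fuller protocol or analysis plan that is not shown. Section 2.10 plans 95% confidence intervals, which will show what a null result excludes.

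Most of that limits the point without removing it. The correction must be treated as inferred, and the absence of an effect size is not itself a fault here. The reversed labels, however, are printed, and so is the step from one-group precision to assured power; a fuller document would not make that step valid.

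The replacement figures also rest on assumptions. Section 2.6 says control data are taken once participation is accepted, with nothing further required, so 15% loss of controls is doubtful; 100 against 127.5 gives 2.80 × √(1/100 + 1/127.5) = 0.37 SD. Section 2.9 has one skinfold observer per paediatric quota, and Section 2.10 plans multivariable models. The simple calculation reflects neither.

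A reader might go further and infer that neither group overlaps the 320 births at all. Section 1 does not support that, since some controls may have been born in the first half of 2017. What holds is that the 320 are not the sampling frame of either group.

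**Conclusion.** The point stands in three parts of differing certainty.

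- **Certain:** the errors are attached to the wrong groups. They should read about 9% for control and 7% for experimental.
- **Conditional:** if a finite population correction for 320 was used, it does not fit these cohorts. It would also describe only a closed set of children, whereas Section 1 aims at routine primary care. With p = 0.5 and 15% loss the margins become about 10.6% (control) and 8.7% (experimental).
- **Certain:** a margin for a proportion in one group gives no basis for the power claim. For the planned comparison the numbers give 80% power at about 0.39 SD after loss in both groups, or 0.36 SD without loss, assuming independent children and a two-sided 5% test.

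A reader might conclude that the sample is too small. The article does not support that: it gives no target difference or SD against which 0.39 SD could be judged. What fails is the word of assurance, because power runs from about 30% to 95% over assumed differences of 0.2 to 0.5 SD.

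**What to change.** In Section 2.5:

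1. Swap the labels so that the larger error belongs to the control group.
2. If the one-group margins are kept, name the formula and the assumed proportion. If a finite population correction was used, drop it and give about 10.6% (control) and 8.7% (experimental).
3. Delete the closing sentence on guaranteed power.
4. State instead that, assuming independent children, a two-sided 5% test and 15% loss in both groups (85 against 127), the design has 80% power for a difference of about 0.39 SD in percentage of fat mass (about 0.36 SD with no loss, 100 against 150), and a 95% confidence interval half-width of about 0.27 SD. Label these figures as dependent on the assumptions.

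This is a text change only. It needs no further participants and no change to procedures. The cost is that the stated precision becomes less favourable if the correction was used.
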